### Trial oversight

The trial will be managed by the Division of Trauma and Surgical Critical Care, Osaka General Medical Center, Osaka, Japan. The data centre is located at the Institute for Clinical Effectiveness, Kyoto, Japan, and data managers will centrally monitor the data through the study period. A steering committee was involved in protocol development and will oversee study progress (Table 2). A Data and Safety Monitoring Board (DSMB) made up of independent experts who are not involved in the conduct of the trial will oversee the safety of the trial and efficacy of the trial therapy and will monitor the integrity and validity of the data collected and the conduct of the clinical trial. A scheduled interim analysis will not be performed in this trial. The data centre will report to the steering committee monthly the numbers of registration and mortality as well as occurrence of serious adverse events. When the absolute difference in mortality becomes greater than five patients or any concerns develop, the steering committee will consult the DSMB on the need for an interim analysis. The DSMB will independently perform the interim analysis and make a recommendation to the steering committee whether to continue the trial.

**Table 2 Tab2:** Study oversight

Role in study	Name	Institution
Principal investigator	[name]	Division of Trauma and Surgical Critical Care, Osaka General Medical Center
Steering Committee		
Steering Committee	[name], PhD	Division of Trauma and Surgical Critical Care, Osaka General Medical Center
Steering Committee	[name], PhD, MPH	Department of Clinical Epidemiology, Hyogo College of Medicine
Steering Committee	[name]	Division of General Medicine, Department of Internal Medicine, Hyogo College of Medicine
Event Adjudication Committee	[name], PhD	Division of Trauma and Surgical Critical Care, Osaka General Medical Center
Event Adjudication Committee	[name]	Kansai Medical University Hospital
Event Adjudication Committee	[name]	Wakayama Medical University Hospital
Data and Safety Monitoring Board	[name], DTM&H	Department of General Internal Medicine and Infectious Diseases, Osaka General Medical Center
Data and Safety Monitoring Board	[name], PhD	Critical Care Medical Center, Faculty of Medicine, Kindai University
Data and Safety Monitoring Board	[name], PhD	Department of Critical Care Medicine, Graduate School of Medicine, Hirosaki University

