### Randomisation and allocation concealment

Patients are randomly allocated to each treatment arm at a 1:1 ratio no earlier than 1 day before starting antibiotic therapy for VAP. Randomisation will be performed with the use of a stochastic minimisation procedure stratified by study centre, presence of chronic obstructive pulmonary disease, presence of traumatic brain injury, presence of post-cardiopulmonary arrest syndrome, and prior antibiotic therapy during the hospitalisation. We will use an electronic data capture system to conduct randomisation and data collection.

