### Sample size

The primary efficacy analysis will assess the non-inferiority of the clinical response of Gram stain-guided antibiotic therapy compared with standard therapy. The margin of non-inferiority is set at 20% on the basis of statistically acceptable tolerance and clinically acceptable margin. This margin was used in previous large clinical trials in the field of critical care [19–21]. Then, the non-inferiority of Gram stain-guided antibiotic therapy is concluded if the upper limit of the one-sided 97.5% CI for the difference in clinical response (standard – Gram stain-guided) is less than 20%. To achieve a power of 80% with an α level of 5%, assuming as stated in the previous study that the clinical response rate is 67.8% with standard therapy and is the same with Gram stain-guided antibiotic therapy (unpublished data), with a non-inferiority margin of − 20%, 86 patients are needed in each group. Assuming 10% non-evaluable patients, we decided to enrol 100 patients per group.

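### The committee running this open-label trial is told of, and must act on, a fixed death-count difference that ignores enrolment and is often crossed by chance; the comparison belongs with the DSMB.

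*Protocol article*

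**What the plan says.** All of the rule stands in the Trial oversight section of the protocol article.

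- No interim look is planned: "A scheduled interim analysis will not be performed in this trial".
- The reporting line runs to the steering committee: "The data centre will report to the steering committee monthly the numbers of registration and mortality as well as occurrence of serious adverse events".
- The trigger is a count: "When the absolute difference in mortality becomes greater than five patients or any concerns develop, the steering committee will consult the DSMB". It is absolute, so it works in either direction, and it is not related to the number of patients enrolled.
- What follows is a consultation: "the steering committee will consult the DSMB on the need for an interim analysis".
- If a look is then held, "The DSMB will independently perform the interim analysis and make a recommendation to the steering committee whether to continue the trial".

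The same section describes the DSMB as independent and as overseeing both safety and efficacy. The article does not say whether the monthly mortality figures are split by arm, masked, or replaced by a yes/no flag. It states no expected mortality.

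**The concern.** Two features of the stated rule work against each other.

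**Who applies it.** A committee cannot act on a between-arm difference in deaths without either seeing the arm totals or being told that the difference has been crossed. Here that committee is the one overseeing conduct of an open-label trial (Design). The Patients section allows exclusion at the study physician's discretion. The Statistical analysis section makes the per-protocol set primary, which depends on who is judged to have a major protocol deviation, and lets the steering committee recommend post hoc analyses. Knowledge of a mortality imbalance during recruitment can influence each of these.

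**How it is scaled.** A six-death gap is a large signal in a small trial and an ordinary fluctuation in a large one. A fixed count checked monthly will therefore often be crossed late in the trial by chance. If so, the committee would often learn of an imbalance that means nothing, and could not easily forget it.

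**Working it through.** **Inputs from the article.** 100 patients per arm (Sample size: "we decided to enrol 100 patients per group"); 1:1 allocation (Randomisation and allocation concealment); alarm at a difference of 6 or more deaths (Trial oversight); recruitment from 1 April 2018 to March 2021, so about 36 monthly reports (Trial status); 28-day follow-up (Assessment and follow-up).

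**Assumed, because the article gives no figure.** True 28-day mortality p, equal in both arms, varied from 10% to 30%; even accrual; deaths spread uniformly over the 28 days.

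**Step 1: the plan's own figure.** The article gives no operating characteristic for the alarm, so the only figure to reproduce is the sample size that fixes the denominator. With response 67.8% in both arms, margin 0.20, one-sided 2.5% and 80% power:

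n = (1.960 + 0.842)² × 2 × 0.678 × 0.322 / 0.20² = 85.7, so 86 per arm, as stated. Allowing for 10% non-evaluable, 86 / 0.9 = 95.6, so 96, which the article rounds up to 100.

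**Step 2: what six deaths mean at different enrolment.** Pooled z = (difference in proportions) / √(2 p̄(1 − p̄)/n).

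- 0 v 6 of 20: p̄ = 0.15, z = 0.30 / √(2 × 0.15 × 0.85 / 20) = 2.66, two-sided p = 0.008 (Fisher exact 0.02).
- 17 v 23 of 100: p̄ = 0.20, z = 0.06 / √(2 × 0.20 × 0.80 / 100) = 1.06, two-sided p = 0.29 (Fisher exact 0.38).

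**Step 3: chance of a gap of 6 or more at one check, equal mortality of 20%.** Exact difference of two binomials:

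| Patients per arm | Gap as percentage points | Chance |
|---|---|---|
| 20 | 30 | 3% |
| 50 | 12 | 17% |
| 100 | 6 | 33% |

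As a cross-check, the standard deviation of the difference at 100 per arm is √(200 × 0.20 × 0.80) = 5.66 deaths, so six is about one standard deviation.

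**Step 4: chance that the alarm is ever raised over the monthly checks, equal mortality.** Simulation of 40,000 trials per scenario. The article uses stochastic minimisation, whose details are not given, so two 1:1 schemes are shown: allocation balanced within successive pairs (lower figure) and a random permutation of 200 (higher figure).

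| Assumed mortality, both arms | Ever crossed at a monthly check | Crossed at one final check |
|---|---|---|
| 10% | 31-33% | 19% |
| 15% | 46-49% | 28% |
| 20% | 56-61% | 33% |
| 25% | 63-70% | 37% |
| 30% | 68-77% | 40% |

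**Step 5: would a strict boundary be a better screen?** With the same monthly checks, the chance of flagging a true excess is:

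| True mortality | Difference above five deaths | Two-sided p < 0.001 |
|---|---|---|
| 20% v 30% | 85-90% | 9% |
| 20% v 40% | 99% | 51-52% |

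The present count is a sensitive referral screen. A p < 0.001 boundary would miss a doubling of mortality about half the time.

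**The case against.** The strongest reply is that this is a referral screen, not a stopping rule. Crossing the threshold makes the steering committee consult the DSMB on whether a look is needed; the DSMB then decides and does any analysis itself. A screen should be sensitive, and a false alarm costs a conversation. That stands, and it removes several stronger readings that a reader might infer:

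- *That the alarm opens an interim analysis or threatens to stop the trial.* The text puts a consultation in between.
- *That early harm below six deaths goes unflagged.* The same sentence also allows referral when any concern arises, serious adverse events are reported monthly, and the DSMB has its own safety remit.
- *That the article states by-arm disclosure.* It does not. Because the difference is absolute, masked arms or a flag from the data centre would be enough to apply the rule. But the article provides neither, and even a flag tells the committee that an imbalance exists.
- *That the lack of a stopping boundary is a defect.* A boundary may sit in a full protocol, analysis plan or DSMB charter that is not shown.
- *That the primary type I error is inflated.* No early non-inferiority claim is described, and stopping for excess deaths does not raise the chance of a false non-inferiority conclusion on clinical response.

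It is also fair that blinded evaluators judge the primary outcome (Outcome measures). That protects the assessment of response. It does not protect recruitment, discretionary exclusion or other conduct decisions.

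What the reply leaves untouched is the recipient of the information and the missing denominator.

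**Conclusion.** The point holds in a limited form and should be corrected. The body that runs an open-label trial is placed in the path of comparative mortality, through a trigger that takes no account of enrolment. Under equal mortality and about 36 monthly checks, it would learn of a chance imbalance in roughly a third of trials at 10% mortality, about half (46-61%) at 15-20%, and 68-77% at 30%. These figures rest on assumed mortality, even accrual and simplified allocation; the article supplies no mortality rate, so no single figure can be called the false-alarm rate. That the committee sees deaths by arm is the natural reading, not a stated fact. The size of any resulting bias in recruitment, exclusion or the per-protocol set cannot be computed from the article.

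**What to change.** In the Trial oversight section:

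1. Send by-arm deaths and serious adverse events to the DSMB only. Give the steering committee pooled counts.
2. Have the DSMB apply the trigger, and read the difference against the number enrolled in each arm. Keep the separate route for any other concern.
3. State that a triggered look covers mortality and safety only and allows no early claim of non-inferiority, so the final one-sided 2.5% level stands.

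Do not replace the referral screen with a p < 0.001 boundary, for the reason shown in the last step of the working.

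The cost is a change of report recipient, a few sentences of wording and slightly more work for the DSMB. Sample size and the primary analysis do not change.

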## Discussion

The GRACE-VAP trial will assess whether initial Gram stain-based restriction of antibiotic therapy is non-inferior to guidelines-based initial broad-spectrum antibiotic therapy in patients with VAP in terms of the clinical response rate. If non-inferiority is achieved, the Gram stain-guided antibiotic choice will be considered to have several advantages in clinical settings. First, Gram staining can be a point-of-care test for selecting antibiotic agents because it should be easy to access at the bedside clinically. Second, it is an inexpensive examination and easy to install in ICUs all over the world, including developing countries. Third, it is easy to learn how to evaluate the results of Gram staining by the method indicated in this trial because we apply merely a simple classification of bacteria.

To the best of our knowledge, this trial will be the first study to answer the clinical question of whether Gram staining can reduce the use of broad-spectrum antibiotics without impairing patient outcomes. We hope that this trial will have a great impact on the establishment of a novel strategy to optimise the use of antibiotic agents safely and restrict the overuse of broad-spectrum antibiotic agents.

## Trial status

The first patient was recruited on 1 April 2018. The last patient is expected to be recruited in March 2021. Osaka General Medical Center provides central trial management and coordination.

## Abbreviations

ATS: American Thoracic Society
DSMB: Data and Safety Monitoring Committee
EOT: End of therapy
FU/TOC: Follow-up/test of cure visit
GNR: Gram-negative rods
GPB: Gram-positive bacilli
GPC: Gram-positive cocci
GRACE-VAP: GRam stain-guided Antibiotics ChoicE for Ventilator-Associated Pneumonia trial
ICU: Intensive care unit
IDSA: Infectious Diseases Society of America
MDR: Multidrug-resistant
MRSA: Methicillin-resistant *Staphylococcus aureus*
VAP: Ventilator-associated pneumonia
